### Randomized groups

#### Cognitive remediation therapy and Teach the Parent (TTP)

This parental involvement addition to CRT is designed to increase parents’ understanding of their adolescent’s thinking styles and reinforce what the adolescent learns about their own style. We hypothesize that by including parents, they will be more likely to challenge eating disorder behaviors and be less likely to accommodate behavioral symptoms of the eating disorder (e.g., make something low-fat for dinner because the adolescent will not be as upset and agrees to eat the low calorie food). In TTP, adolescents receive their own treatment manual to use during their CRT sessions with their parents. Adolescents do tasks with their parents that they have already done with study staff. Adolescents are instructed to explain the rationale for CRT, what they have learned, and do four tasks with their parents. Table 2 lists the tasks done during each TTP session. The family is instructed to refrain from speaking about the eating disorder during CRT. TTP sessions occur up to four times (every other CRT session). A research assistant will be on hand to observe the session and ensure that the adolescent presents at least two tasks to parents. However, the research assistant will not engage with the family.

#### Cognitive remediation therapy and contact control (Family Fun Time, FFT)

In order to assess for any non-specific effects of spending non-eating disorder driven time with family, adolescents in the CRT + contact control condition will be asked to spend 3–4 sessions with their parents engaging in fun activities (games, coloring, trivia). We refer to this condition as CRT + Family Fun Time (CRT + FFT). The family is provided with the rationale that engaging in imaginative and fun play can help to stimulate brain development. Tasks were chosen to be engaging and superficially relevant to CRT (see Table 2 for a list of session-specific TTP and FFT tasks). As with TTP, adolescents are provided with an FFT manual and are asked to guide their parent through the session. Specific tasks are laid out each session and adolescents are provided with the necessary materials. As with TTP, the family is asked to refrain from eating disorder talk. Research assistants will be on-hand to observe interactions but will not engage with the family.

#### Treatment at usual

Adolescents in this condition will not receive any experimental intervention. They will have a standard hospital stay with all normal contact with a multidisciplinary team of health professionals: attending physician, psychologist, social worker, and dietician. Medical stabilization for adolescents with AN at CHOP has been described elsewhere [51].

### Blinding and randomization

The adolescent and at least one parent are required to participate in the study. After baseline assessment is completed (see Table 4 for measurement schedule according to the SPIRIT guidelines [53, 54]), the adolescent is randomized to a condition. Research assistants completing the baseline assessment are therefore blind to the condition at baseline.

**Table 4 Tab4:** Schedule of enrollment, intervention, and assessment

Study period													
	Enrollment	Baseline		Randomization	CRT sessions/intervention	Discharge		4 weeks post-discharge		3 months post-discharge		6 months post-discharge	
Timepoint	− t_1_	T_1_		T_1a_	Up to 8 sessions No assessment	T_2_		T_3_		T4		T5	
Enrollment													
Eligibility screen	X												
Informed consent	X												
Randomization				X									
Intervention													
CRT + TTP					X								
CRT + FFT					X								
TAU					X								
Assessments													
		*Adol.*	*Par.*			*Adol.*	*Par.*	*Adol.*	*Par.*	*Adol.*	*Par.*	*Adol.*	*Par.*
*Diagnostic/symptom tracking*													
EDE [55]		X								X			
EDE-Q [70]		X						X		X		X	
EDE-SF [52]		X				X		X		X		X	
ABOS [71]			X						X		X		X
BASC-2[72]		X	X					X	X	X	X	X	X
Weight and height								X		X		X	
*Medical chart review*													
Weight history		X											
Current weight		X				X		X		X		X	
Hormone levels		X								X		X	
Vital signs		X				X		X		X		X	
Daily caloric intake		X				X				X		X	
*Neuro-psychological*													
WASI (2 scale) [73]		X	X										
D-Kefs [74]		X	X							X	X		
BRIEF [75]		X	X					X	X	X	X	X	X
Hayling [76]		X	X							X	X		
Rey-O [77]		X	X							X	X		
Brixton [76]		X	X							X	X		
Line bisection [78]		X	X			X	X	X	X	X	X	X	X
PennCNB [79]		X	X									X	X
*Questionnaire*													
C/E [80]		X	X			X	X						
MSCARED [81]		X	X			X	X	X	X	X	X	X	X
EDQoL [82]		X				X		X		X		X	
DBS [83]		X				X		X		X		X	
CFS [84]		X	X			X	X			X	X	X	X
DFlex [85]		X	X			X	X	X	X	X	X	X	X
C-FOCI [86]		X				X				X		X	
YBC-EDS-SRQ [87]		X						X		X		X	
AFQ-Y [88]		X								X		X	
AAQ [89]			X						X		X		X
AESED [90]			X						X		X		X
BIS/BAS [91]		X	X					X	X	X	X	X	X
PAAQ [92]			X						X		X		X
DASS-21 [93]			X						X		X		X
FQ [94]			X						X		X		X
IES [95]			X						X		X		X

Note. *Adol.* adolescent, *Par.* parent, *TAU* treatment as usual, *CRT + TTP* cognitive remediation therapy + Teach the Parent, *CRT + FFT* cognitive remediation therapy + Family Fun Time, *EDE* Eating Disorder Examination, *EDE-Q* Eating Disorder Examination Questionnaire, *EDE-SF* Eating Disorder Examination Short Form, *ABOS* Anorectic Behavior Observation Scale, *BASC* Behavior Assessment System for Children-2, *WASI* Wechsler Abbreviated Scale of Intelligence, *D-Kefs* Delis-Kaplan Executive Functioning Scales (Trail Making, Verbal Fluency, Color-Word Interference, & Sorting), *BRIEF* Behavior Rating Inventory of Executive Function, *Rey-O* Rey-Osterrieth Complex Figure Test, *PennCNB* computerized neuropsychological battery, *C/E* Credibility/Expectancy Questionnaire, *MSCARED* Motivational Stages of Change for Adolescents Recovering from an Eating Disorder, *EDQoL* Eating Disorder Quality of Life, *DBS* Decisional Balance Scale, *CFS* Cognitive Flexibility Scale, *DFlex* Detail and Flexibility Questionnaire, *C-FOCI* Children’s Florida Obsessive Compulsive Inventory, *YBC-EDS-SRQ* Yale-Brown-Cornell Eating Disorders Self-report, *AFQ-Y* Action Fusion Questionnaire—Youth, *AAQ* Acceptance and Action Questionnaire, *AESED* Accommodation and Enabling Scale for Eating Disorders, *BIS/BAS* Behavioral Inhibition System and Behavioral Activation System Scales, *P-AAQ* Parental Acceptance and Action Questionnaire, *DASS-21* Depression Anxiety and Stress Scale-21, *FQ* Family Questionnaire, *IES* Impact of Events Scale

Randomization was obtained via block randomization using values from Research Randomizer, an online randomization program (http://www.randomizer.org/). An undergraduate research intern completed the randomization prior to recruitment starting, wrote the condition number on an index card, and sealed the index card in a security envelope. Envelopes are numbered consecutively. As participants consent to participate, they are assigned the next number and that envelope is pulled and put in their research chart. Once assessment is complete, the envelope is opened and the condition recorded in a password protected file.

The majority of follow-up assessments (T_2_, T_3_, and T_5_) are primarily questionnaire based. Families return at T_4_ to complete the neuropsychological battery. Research assistants who conduct the assessments at this time point are not specifically blinded to condition; however, they are also not informed of the family’s experimental condition. As research assistants open the randomization envelopes, they may independently recall a family’s condition. Data analysis (see below) will be blinded. The statistician and PI (DR and CAT, respectively) will not be aware of the coding for condition until after data analysis is complete. The study coordinator will code the data and be responsible for keeping the investigators blind.

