### Description of investigational intervention

The principles of cognitive remediation therapy are the same across studies; however, CRT protocols often vary in terms of the tasks used. This trial uses a modified version of an adolescent manual developed by [name] [47]. The CRT tasks included in our manual are delineated in Table 1. CRT sessions occur daily (excluding weekends) for 45–60 min every day while adolescents are in hospital, for up to 8 days. We have set an a priori definition of “treatment completion” as six sessions of CRT. Treatment completion for parent involvement component was set a priori at three sessions of either TTP or FFT. Though the median length of stay in hospital is 10 days, it is possible that adolescents may discharge before completing all sessions of CRT. These adolescents will continue to complete all study procedures (i.e., follow-up) but will not be considered treatment completers for feasibility assessment (what percentage of adolescents complete CRT) or data analysis (secondary goals).

Study interventionists include the PI or a graduate student under the PIs supervision. [name] provided initial training in CRT, and will provide supervision and feedback to the PI throughout the study duration. CRT sessions will be audio-recorded and coded for adherence to the manual. Should a study interventionist deviate from the manual (e.g., do tasks out of order), this will be noted in the data set. The interventionist will be informed and further training provided to ensure adherence.

CRT sessions are administered every weekday while the adolescent is in hospital, are conducted in an individual format, and tasks are delivered in a standard order to ensure consistency. Table 1 lists all tasks in the standardized order in which they are presented each session. Table 1 also notes the session in which the task occurs; most tasks are administered in each session. It is possible that not all tasks will be able to be administered due to time constraints or individual variables (i.e., hand flip if the adolescent has an IV). At the end of the pilot study, we will re-evaluate the tasks and determine if all should be included a final manual.

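### The analysis is described as blinded and the investigators as kept blind, but the PI delivers or supervises all CRT, and the 3-month assessors' knowledge of arm is only partly acknowledged

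*Protocol article*

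**What the plan says.** Blinding and randomization makes three linked statements about the analysis. "Data analysis (see below) will be blinded". The statistician and the PI "will not be aware of the coding for condition until after data analysis is complete". And "The study coordinator will code the data and be responsible for keeping the investigators blind".

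Description of investigational intervention sets out who delivers the treatment: "Study interventionists include the PI or a graduate student under the PIs supervision". The external trainer "will provide supervision and feedback to the PI throughout the study duration".

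For the 3-month visit, Blinding and randomization says that the research assistants who assess are not specifically blinded, and in the same sentence that they are not told the family's arm. It then adds: "As research assistants open the randomization envelopes, they may independently recall" a family's condition.

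The two arm descriptions give research assistants another task. In Teach the Parent (TTP), "A research assistant will be on hand to observe the session". In Family Fun Time (FFT), "Research assistants will be on-hand to observe interactions but will not engage with the family".

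On baseline, Blinding and randomization says that assessors are blind because randomization follows the assessment. Measurement strategy allows the EDE and the self-report battery to be finished after randomization.

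**The concern.** Someone who treats the CRT families, or supervises the person who does, knows who received CRT. Withholding the arm code from the dataset does not change that. A report that repeats the protocol's wording would credit the trial with protection it does not have where the PI is concerned.

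A separate and smaller issue arises at 3 months. The EDE is an interview, and the neuropsychological tests are given by an examiner. If that examiner opened the family's envelope or sat in on its parent sessions, the arm is known, and administration or scoring could drift in favour of CRT.

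These results count for something. Change in set-shifting or central coherence is a listed secondary goal, and the Discussion lets trends on secondary outcomes inform whether the work is scaled up.

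**Working it through.** No figure in the protocol bears on this point, so the check is a comparison of sections plus one count.

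**1. What the PI can know.**
- The only interventionists named are the PI and a graduate student whom the PI supervises. All CRT is therefore delivered by the PI or under the PI's supervision.
- Power analysis plans 20 per group in three groups: 3 × 20 = 60.
- The two CRT arms hold 2 × 20 = 40. The remainder is 60 − 40 = 20, who are identifiable as usual care by elimination.
- Table 1 has the family told its condition in session 1 and has the parent sessions reviewed in CRT sessions 3, 5 and 7. An interventionist therefore also learns whether a CRT family is in TTP or FFT.

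The statement about the coordinator cannot be true of the PI as a person. What can be true is that the PI is not told which dataset label stands for which arm.

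**2. How strong a masked label would be.**
- Data management and analysis plan keeps the file linking study codes to participants in the PI's research lab and gives the PI access to the data drive. A person who knows who had CRT could work out the labels.
- Description of investigational intervention has departures from the manual noted in the dataset and uses six-session completer status in the secondary analyses. CRT session data can exist only in the CRT arms, so these fields would separate CRT from usual care even for the statistician if supplied with the labels.

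**3. The 3-month assessors.**

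| Statement | Section | Consequence |
|---|---|---|
| Assessors not specifically blinded | Blinding and randomization | Open assessment is admitted |
| Assessors not told the arm | Same sentence | Untrue of any assessor who opened that family's envelope |
| Research assistants open envelopes and may recall | Next sentence | First route, disclosed |
| Research assistants observe TTP and FFT sessions | The two arm descriptions | Second possible route, not mentioned under blinding |

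No section says that the observer of a family also assesses it at 3 months, and none prevents it.

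**4. Which outcomes are exposed.** In Table 4 the 3-month visit is the only post-baseline occasion for the EDE, D-KEFS, Hayling, Brixton and Rey-O. The primary outcomes are recruitment, completion, refusal, retention and time to complete measures. The three MANOVA variables are engagement, weight gain and accommodation. Table 4 lists its motivation and accommodation instruments as questionnaires, and weight is measured. None of these is an examiner-scored 3-month test.

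**5. Baseline.** The assessor's blindness is derived from the order of events, assessment first and randomization second. Measurement strategy relaxes that order for the EDE, so the derivation fails for any EDE done after the envelope is opened.

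**The case against.** The case against has real force on four points.

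- **Assessors.** A reader might infer that the protocol falsely claims blind 3-month assessors. It does not: it says they are not specifically blinded and itself raises the envelope problem. What remains is a loose phrase and an unlisted second route.
- **Same individuals.** A reader might also take it as fact that those who observe a family go on to assess it. That is an inference; the text only leaves it possible.
- **The PI sentence.** Read literally, it promises ignorance of the dataset coding, and labels can be masked for someone who knows allocations. This stands, but it does not rescue the broader statement that the investigators are kept blind. Nor does the PI's role contradict the statistician's blinding.
- **Consequence.** The feasibility outcomes and the MANOVA variables lie outside the problem, and the Discussion says cognitive flexibility is not of primary interest. It is tempting to assume an examiner shift and convert it to an inflated error rate for pooled CRT against usual care. The protocol gives no such shift and plans no such pooled test on these measures, so a figure of that kind would carry no weight.

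The remedy also has limits. Families know their arm and may tell any assessor, and whether staffing suffices is itself one of the pilot's questions.

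**Conclusion.** The point holds in limited form. The claim that the investigators are kept blind does not fit the PI's role as interventionist and supervisor. For the PI only masked labels are possible, and these are weak. This assumes that the PI knows who is enrolled and, through supervision, whom the student treats; both follow naturally from the roles described.

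The 3-month assessment is an admitted open assessment with one inconsistent phrase and one unmentioned route to the arm. The risk is detection bias in the 3-month EDE and the set-shifting and central-coherence tests. Its size cannot be estimated from the document. The baseline blinding statement is not secured for an EDE done after randomization.

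The correction is worth making because it is cheap and because secondary trends inform the decision to scale up. It does not threaten the primary feasibility aim.

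**What to change.** 1. **Analysis.** Limit the blinding claim to the statistician, working from masked arm labels, with session and completer data withheld until the planned comparisons have been run. State that the PI knows allocations through treatment and supervision and makes no analysis decisions before that point.
2. **Envelopes.** Have the coordinator, who already codes the data, open the envelopes and record the arm in place of the research assistants.
3. **3-month visit.** Where existing staffing allows, give the EDE and neuropsychological testing to a research assistant who did not observe that family's TTP or FFT sessions. Record at each visit whether the assessor knows the arm. Where this cannot be arranged, describe the assessment plainly as unblinded. In either case remove or qualify the statement that assessors are not informed, and name session observation as a possible route.
4. **Baseline.** Reconcile the statement that baseline assessors are blind with the allowance for an EDE after randomization, for example by restricting the statement to assessments completed before the envelope is opened.

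The cost is rewording, reassignment of tasks among existing staff and one extra item on the visit form. The downside is some constraint on rostering and a weaker, but true, blinding claim. No new measures, participants or posts are needed.

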### Measurement strategy

As this is a pilot and feasibly RCT, we chose a comprehensive measurement battery that closely resembles batteries used in prior research investigating set-shifting, central coherence, and CRT in individuals with AN. See Table 4 for all measures and the measurement schedule. A goal of the study was to evaluate the utility of the battery and streamline it for future research. Both parents and the adolescent complete a standard self-report questionnaire battery, neuropsychological assessment, and IQ assessment. In addition, the adolescents complete a semi-structured diagnostic interview to assess eating disorder symptoms (Eating Disorder Examination, EDE [55]). We included measures designed to assist us in evaluating our outcome variables. As neurocognitive inefficiencies are hypothesized to be endophenotypes [7, 37], we included IQ and neuropsychological assessment of both adolescent and parents. Baseline assessment is comprehensive and typically lasts a significant portion of the day. Families are informed of the length of the intake during the screening phase.

As the adolescents are in hospital, the baseline assessment can occur over multiple days. For adolescents, the neuropsychological assessment is prioritized, as we want to be able to assess for any impairment that may be present when acutely underweight. Randomization occurs once neuropsychological assessment is complete; it is possible that the EDE and self-report may not be completed until after randomization. Parent neuropsychological and IQ assessment is scheduled at the parents’ convenience throughout the week that their child is in hospital. If parents are not able to complete the IQ assessment at baseline, it can be administered at 3 months post-discharge as parental IQ is expected to be stable.

In order to facilitate participant retention and to reduce burden on families, all baseline assessments will take place while participant is in hospital. After consent is obtained, all participants will be given baseline questionnaires and the baseline assessment scheduled. The pre-discharge assessment questionnaires are given the day before or the day of discharge. Every effort will be made to collect both discharge questionnaires prior to the participant discharging. Follow-up assessment can be completed either on-line (via RedCap) or via pen and paper questionnaires mailed to families. When neuropsychological assessment needs to occur, we coordinate assessment with normal medical or behavioral health follow-up.

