**Fig. 1 Fig1:**
[figure not shown]
Study flowchart/timetable for data collection

After consent is obtained and baseline assessment is completed, participants are randomized to one of three groups: CHOP’s standard care (treatment as usual; TAU), CRT + contact control (known as “Family Fun Time”), and CRT + Teach the Parent. Those randomized to one of the CRT conditions will receive individual sessions of CRT daily (excluding weekends) while in hospital. Follow-up will be naturalistic. All attempts will be made to follow participants whether they enter outpatient treatment or are referred to a higher level of care. Psychosocial, neurocognitive, medical, and behavioral measures will be collected throughout the study. Group differences will be evaluated at each of the five assessment time points.

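### The protocol gives two incompatible orders for baseline and randomisation, so some baseline questionnaires behind the secondary efficacy analyses may be completed after allocation and the statement of blind baseline assessment is not secured

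*Protocol article*

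**What the plan says.** Four places in the protocol article put baseline first.

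- Study design, text under Fig. 1: "After consent is obtained and baseline assessment is completed, participants are randomized to one of three groups".
- Blinding and randomization, opening paragraph: the adolescent is randomised after baseline, and "Research assistants completing the baseline assessment are therefore blind to the condition at baseline".
- Blinding and randomization, on the envelopes: "Once assessment is complete, the envelope is opened and the condition recorded in a password protected file".
- Table 4: every baseline measure, including the EDE and the questionnaires, stands at T1, ahead of randomisation at T1a.

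Measurement strategy says otherwise: randomisation waits only for the neuropsychological tests, and "it is possible that the EDE and self-report may not be completed until after randomization". The same section schedules the parents' neuropsychological and IQ tests at their "convenience throughout the week that their child is in hospital".

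On who learns the allocation, Blinding and randomization adds: "As research assistants open the randomization envelopes, they may independently recall" a family's condition. Table 1 places telling the family its condition in CRT session 1.

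**The concern.** The blinding statement is a deduction from the order of events. If the EDE, a semi-structured interview, can be held after the envelope is opened, the deduction fails for that interview. The person holding it may be the person who opened the envelope.

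For the questionnaires the issue is the respondent. An adolescent or parent who completes a baseline form late may already know the condition, or may already have had a session. Efficacy analysis uses baseline as the reference for change, and in the latent growth curve models the level factor represents baseline. A baseline value influenced by allocation then enters the estimated change directly.

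Efficacy is secondary in this pilot, but the order still matters. Piloting the randomisation procedures and the assessment battery is part of the stated primary aim. The Discussion also lets the presence or absence of a trend on the secondary outcomes bear on whether a larger trial is feasible.

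**Working it through.** **1. Can the statements be read together?** The envelope sentence could be rescued by taking its word for assessment to mean the neuropsychological tests only. That reading does not rescue Study design or Table 4, which place the whole baseline before randomisation. Nor does it rescue the blinding sentence, which covers the baseline assessment without exception. Measurement strategy also says that questionnaires are handed out after consent, but it sets no deadline for their return before randomisation. The conflict stays.

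**2. Which efficacy outcomes are exposed?** Efficacy analysis names three dependent variables.

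| Variable | Baseline source | Exposed? |
|---|---|---|
| Symptom accommodation | AESED, parent questionnaire (Table 4) | Yes, if the self-report that may run late includes parents' forms |
| Treatment engagement | Instrument not named; MSCARED is inferred from the Discussion's mention of stages of change | Yes, if it is a questionnaire |
| Weight gain | Medical chart review (Table 4) | No |

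The sentence on late completion follows one about adolescents. Extending it to parents rests on the same section's description of a self-report battery completed by both parents and adolescents. Adolescent self-report is covered on any reading.

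**3. Is there another pre-follow-up value to fall back on?** In Table 4 the AESED is taken at baseline, 4 weeks, 3 months and 6 months, and not at discharge. Baseline is therefore its only value before follow-up. The MSCARED is also taken at discharge, but that is after the intervention.

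**4. Parent neuropsychological tests.** Table 2 has parents do a Stroop task and a geometric-figure task in TTP session 1. The parent battery in Table 4 and its note includes D-KEFS Color-Word Interference and the Rey-Osterrieth figure. A parent tested late in the week in the TTP arm may already have practised similar tasks, and FFT parents do not do these tasks. These tests are not among the three dependent variables. They matter for the parent neuropsychological comparisons between baseline and 3 months.

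**5. Size.** The documents give neither the share of late baselines nor the shift in them, so this is illustration only. Let D be the true between-arm difference at follow-up, p the share of baselines taken late, and q the share of D already present in a late baseline.

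- Expected baseline difference = p × q × D
- Expected difference in change = D − p × q × D = D × (1 − p × q)

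| p (assumed) | q (assumed) | 1 − p × q |
|---|---|---|
| 0.1 | 0.1 | 1 − 0.01 = 0.99 |
| 0.3 | 0.25 | 1 − 0.075 = 0.925 |
| 0.5 | 0.5 | 1 − 0.25 = 0.75 |

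If early exposure moves answers the other way, q is negative. This could happen if an introduction to CRT makes parents report more accommodation than they otherwise would. With p = 0.3 and q = −0.25 the factor is 1 + 0.075 = 1.075, an inflation. The direction is therefore open as well.

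**6. The plan's own power figure.** The stated power of .55 for the mixed MANOVA reproduces. With N = 60, three groups, five measures, f = .25 and α = .10:

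- noncentrality = 60 × 2 × 0.0625 = 7.5
- degrees of freedom = 2 × 4 = 8 and 2 × (60 − 3 − 4 + 2) = 110
- power = 0.551

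This point does not alter that figure.

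**The case against.** The strongest reply is that little depends on these scores. The primary outcomes are recruitment, completion, refusal, retention and time to complete measures, and none uses a baseline score. The article says that testing of the efficacy hypotheses will be limited. Late completion is worded as a possibility, forms go out straight after consent, and a form returned between randomisation and CRT session 1 may be unaffected. All of this stands, and it sets the severity. It does not remove the contradiction.

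A second reply concerns cost. The median stay is 10 days, sessions run on weekdays only, and completion means six sessions. If identification takes the full 48–72 h and consent a further 12–24 h, 2.5 to 4 days are gone. That leaves 10 − 4 = 6 to 10 − 2.5 = 7.5 calendar days, or 4 to 5.5 weekdays if a weekend falls in that period. Holding the envelope for the whole baseline, including the EDE, could cost sessions and depress a primary feasibility outcome. This also stands, and it is why the fix is limited to the short outcome questionnaires.

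Some stronger readings are tempting but not supported:

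- **Only the CRT arms are contaminated.** Late completion is allowed in every arm, and nothing says that TAU families stay unaware of their allocation. Bias needs a shift that differs between arms. A shift common to TTP and FFT would largely cancel in that comparison.
- **Baseline is spoiled as a covariate.** No baseline-adjusted analysis is described.
- **Eligibility is compromised by a late EDE.** Screening is by medical record, and no passage makes the EDE the eligibility test.

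**Conclusion.** The contradiction is certain, because it lies in current text. Measurement strategy permits an order that Study design, Blinding and randomization and Table 4 exclude, and the inference to blind baseline assessment fails wherever that permission is used.

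The consequence for results is possible and of unknown size. It rests on three assumptions: that some outcome questionnaires are in fact completed late, that the self-report in question includes the parents' AESED, and that engagement is measured by a questionnaire such as the MSCARED. Under the assumed values above, change from baseline could be attenuated by 1% to 25%, or inflated if early exposure moves answers the other way. A reader might infer that every planned comparison is invalid. That goes too far: weight is unaffected, the primary feasibility outcomes do not use these scores, and the share of late forms may be small.

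Severity is moderate. The passages should be reconciled and the outcome questionnaires protected.

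**What to change.** 1. In Blinding and randomization and in Measurement strategy, require the AESED and the engagement measure, to be named, to be completed together with the adolescent neuropsychological tests before the envelope is opened.
2. Let the EDE and the remaining questionnaires follow if needed. Where possible, have the EDE done by an assessor who has not opened the envelope.
3. Record the completion date of each baseline form and parent test relative to envelope opening and to the first CRT, TTP or FFT session.
4. Add a sensitivity analysis that treats values obtained after randomisation as missing baseline. Keeping this as a sensitivity analysis avoids discarding data from the main analysis at 20 per arm.
5. Correct the order statements in Study design and Blinding and randomization. Limit the blinding sentence to assessments made before the envelope is opened.

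Cost: a reordering of the baseline battery, date recording and one extra analysis, with no new measure. Randomisation may be slightly delayed for some families. The EDE provision depends on a second assessor being available.
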